## 5. Outcome Measures

Primary outcome measures:

- Time to clinical improvement (defined as time from randomization to either an improvement of two points on a 10-category ordinal scale or discharge from the hospital, whichever came first):

| Patient State                   | Descriptor                                                                                                          | Score |
|---------------------------------|---------------------------------------------------------------------------------------------------------------------|-------|
| Uninfected                      | Uninfected; no viral RNA detected                                                                                   | 0     |
| Ambulatory (Mild Disease)       | Asymptomatic; viral RNA detected                                                                                    | 1     |
|                                 | Symptomatic; independent                                                                                            | 2     |
|                                 | Symptomatic; assistance needed                                                                                      | 3     |
| Hospitalised (Moderate Disease) | Hospitalized, not oxygen therapy                                                                                    | 4     |
|                                 | Hospitalized; oxygen by mask or nasal prongs                                                                        | 5     |
| Hospitalised (Severe Disease)   | Hospitalized, oxygen by NIV or high flow                                                                            | 6     |
|                                 | Intubation and mechanical ventilation, $\text{PaO}_2/\text{FiO}_2 \geq 150$ or $\text{SpO}_2/\text{FiO}_2 \geq 200$ | 7     |
|                                 | Mechanical ventilation $\text{PaO}_2/\text{FiO}_2 < 150$ ( $\text{SpO}_2/\text{FiO}_2 < 200$ ) or vasopressors      | 8     |
|                                 | Mechanical ventilation $\text{PaO}_2/\text{FiO}_2 < 150$ and vasopressors, dialysis, or ECMO                        | 9     |
| Dead                            | Dead                                                                                                                | 10    |

Abbreviations: ECMO, Extracorporeal membrane oxygenation; NIV, Non-invasive ventilation;  $\text{FiO}_2$ , Fraction of inspired oxygen;  $\text{PaO}_2$ , pressure of arterial oxygen;  $\text{SpO}_2$ , oxygen saturation

- Time to PCR negativity. Proportion of participants with SARS-CoV-2 polymerase chain reaction (PCR) negative result at Days 7, 10, 14 and 28.
- Temporal patterns of SARS-CoV-2 viral load quantified by RT-PCR from nasal swabs or sputum of patients receiving SOC alone versus SOC plus study drug.

Secondary outcome measures:

- Time to symptoms resolution as monitored by the inFLUenza Patient-Reported Outcome (FLU-PRO) questionnaire with some modifications for COVID-19 (Appendix 8).
- Clinical status as assessed with the 10-category ordinal scale on days 7 and 14
- Duration of hospitalization in survivors
- Day 28 mortality
- Time from treatment initiation to death
- Proportion with viral RNA detection over time

 Note:  $\text{PaO}_2/\text{FiO}_2$  of 200-300, mild ARD; 100-200, moderate ARD; <100, severe ARD

Safety outcome measures:

- Adverse events during treatment
- Serious adverse events (respiratory failure or Acute Respiratory Distress Syndrome (ARDS), acute kidney Injury (AKI), secondary infection, shock, severe anemia, acute gastritis, unconsciousness, sepsis, acute heart failure)
- Gastrointestinal adverse events (nausea, vomiting, and diarrhea)
- Premature discontinuation of treatment

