| Entry vital signs                                     | X     |       |       |       |          |       |          |        |            |        |        |        |
| Eligibility confirmation                              | X     |       |       |       |          |       |          |        |            |        |        |        |
| Enrolment                                             | X     |       |       |       |          |       |          |        |            |        |        |        |
| Safety blood (10 mL)                      | X     |       |       |       |          | X     |          |        |            | X      |        |        |
| Dispense standard of care                             | X     |       |       |       |          |       |          |        |            |        |        |        |
| Randomisation                                         | X     |       |       |       |          |       |          |        |            |        |        |        |
| Dispense trial intervention (BID for 14 days)         |       | X     | X     | X     | X        | X     | X        | X      | X          | X      |        |        |
| Daily vitals, including SpO 2              |       | X     | X     | X     | X        | X     | X        | X      | X          | X      | X      | X      |
| Flu-PRO                                               |       | X     | X     | X     | X        | X     | X        | X      | X          | X      | X      | X      |
| Clinical improvement assessment                       |       | X     | X     | X     | XXX      | X     | XX       | X      | XXX        | X      | X      | X      |
| Saliva or swab collection for SARS-CoV-2  | X     |       | X     |       | X        | X     |          |        |            | X      |        | X      |
| Pharmacokinetic sampling                  |       |       | X     |       | XXX      | X     |          |        |            | XX     |        |        |
| Adverse event monitoring                              |       | X     | X     | X     | X        | X     | X        | X      | X          | X      | X      | X      |
| Study exit assessment                                 |       |       |       |       |          |       |          |        |            |        |        | X      |

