 10 mL blood draws each at baseline, day 7 and day 14 will be used to assess essential biochemical (including AST, ALT) and haematology (including XXX) safety parameters.

 Sampling schedule for SARS-CoV-2 viral load: Days 0, 2, 4, 6, 7, 14, and 28.

 Sparse PK sampling in all patients paired with saliva sample for SARS-CoV-2 viral load, as well as intensive PK sampling on days 5 and 14 in 12 selected participants.

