## 6. Power and Sample Size Determination

As shown in Figure 3, the sample size estimation is based on the assumption that an improvement of at least 60-80% in time to SARS-CoV-2 PCR negativity and symptoms resolution can be achieved in the intervention group compared with the control group. Hence, a total sample size of 89 will provide at least 80% power to show or exclude 60% improvement in time to SARS-CoV-2 PCR negativity. This assumes a two-sided and 5% type 1 error rate. Therefore, providing for a 10% loss to follow up rate, a total of 98 patients will be recruited.

[figure not shown]

**Figure 3.** Power calculation and sample size estimation.

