## 12. Statistical Considerations

Proportion of participants with SARS-CoV-2 PCR negative result at days 7, 14 and 28 will be compared between the intervention and control groups. Analysis of clinical improvement based on the 10-category ordinal scale will be performed using time-to-event data (patients will be censored at 28-days of follow-up). Categorical variables will be analysed using the log-rank test and continuous variables will be assessed using a univariable Cox proportional hazard regression analysis. Analysis of cumulative improvement rate will be presented by Kaplan-Meier survival curves when independent variables are dichotomous or categorical. A univariable Cox regression analysis will be conducted and covariates with a  $p < 0.25$  in the univariable analysis will be included in the multivariable model. These analyses will be conducted using Stata®.

An interim analysis of data from the Pilot Stage will be conducted after the first 30 participants have completed days 1-14 of the study period. These data will provide valuable insights regarding the design, conduct and analysis of the Pivotal Stage, including sample size estimate, intervention-responsive definition of the primary and secondary endpoints, and procedures to enhance quality of trial conduct. The Trial Steering Committee will make timely recommendations for finalizing the design of the Pivotal Stage based on data from the Pilot Stage. To preserve the integrity of the Pivotal Stage, data from the Pilot Stage would only be included in the primary analyses of the Pivotal Stage data only if those using the Pilot Stage data to enlighten decisions about finalizing the design of the Pivotal Stage do not have access to information from the Pilot Stage that would be directly or indirectly informative about the efficacy and safety of the experimental regimens being evaluated in the Pivotal Stage.

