## 13. Assessments of Nitazoxanide Pharmacokinetics

Following oral administration of 500 mg of nitazoxanide every 12 hours for 7 consecutive days in adults, the mean (SD)  $C_{max}$  of tizoxanide was 10.6 (2.1)  $\mu\text{g/mL}$  and no significant accumulation of nitazoxanide metabolites tizoxanide or tizoxanide glucuronide was detected. In a study that investigated nitazoxanide efficacy for pulmonary tuberculosis, a 1000 mg twice daily dose for 14 days was employed and no grade 4 or 5 adverse event was observed. The  $C_{max}$  of tizoxanide on days 5 and 14 were 11.3 (4.6)  $\mu\text{g/mL}$  and 9.0 (4.1)  $\mu\text{g/mL}$ , respectively. Therefore, to characterise the exposure-response relationship of tizoxanide when 1000 mg nitazoxanide is taken two times daily in combination with 300/100 mg atazanavir/ritonavir, pharmacokinetic (PK) sampling will be performed in trial participants on days 5 and 14 (intensive) and on days 3, 7, 10, 21, and 28 (sparse) based on the following schedule:

| Specimen               | Intensive pharmacokinetic (PK) sampling (n = 12)                                                | Sparse PK sampling (n = 49)                                                                                                                                                                    |
|------------------------|-------------------------------------------------------------------------------------------------------------|------------------------------------------------------------------------------------------------------------------------------------------------------------------------------------------------|
| Dried Blood Spot (DBS) | 0.5, 1, 2, 4, 6, 8 and 12 hours after dose on day 5
0.5, 1, 2, 4, 6, 8 and 12 hours after dose on day 14 | 12 hours after dose on day 2
12 hours after dose on day 4
12 hours after dose on day 6
12 hours after dose on day 7
12 hours after dose on day 14
12 hours after dose on day 28 |
| Saliva                 | 0.5, 1, 2, 4, 6, 8 and 12 hours after dose on day 5
0.5, 1, 2, 4, 6, 8 and 12 hours after dose on day 14 | 12 hours after dose on day 2
12 hours after dose on day 7
12 hours after dose on day 14                                                                                                  |

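### The primary PCR outcome names Day 10, but no viral sample is scheduled between Day 7 and Day 14, and the analysis section leaves Day 10 out

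*Protocol*

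**What the plan says.** Five places in the protocol bear on when PCR status is known.

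- **Trial Synopsis and Section 5 (primary outcomes).** Under time to PCR negativity, both give: "Proportion of participants with SARS-CoV-2 polymerase chain reaction (PCR) negative result at Days 7, 10, 14 and 28".
- **Table 1 (Section 4).** The row "Saliva or swab collection for SARS-CoV-2" is marked at Day 0, Day 2, Days 4-6, Day 7, Day 14 and Day 28. The columns for Days 8-9, Day 10 and Days 11-13 are blank.
- **Table 1, footnotes 2 and 3.** Footnote 2 fixes the days: "Sampling schedule for SARS-CoV-2 viral load: Days 0, 2, 4, 6, 7, 14, and 28". Footnote 3 ties the pharmacokinetic (PK) samples to them: "Sparse PK sampling in all patients paired with saliva sample for SARS-CoV-2 viral load".
- **Section 12.** "Proportion of participants with SARS-CoV-2 PCR negative result at days 7, 14 and 28 will be compared between the intervention and control groups". Day 10 is absent and no reason is given.
- **Section 13.** The text places sparse PK sampling "on days 3, 7, 10, 21, and 28 (sparse"), while the table directly below lists dried blood spots on Days 2, 4, 6, 7, 14 and 28.

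Section 6 sizes the trial on the same endpoint: "a total sample size of 89 will provide at least 80% power to show or exclude 60% improvement in time to SARS-CoV-2 PCR negativity".

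**The concern.** A proportion negative at Day 10 needs a Day 10 specimen. None is scheduled, and no analysis plan can supply one afterwards. As written, the trial must either report a primary time point as wholly missing or drop it without explanation. In an open-label trial with several primary outcomes, an unexplained change to one of them is awkward to defend.

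The second problem follows from the same schedule. Time to PCR negativity is known only to within the interval between two samples. The protocol takes samples on consecutive days (6 and 7) and then leaves a week with none. A participant who clears on Day 8 and one who clears on Day 13 give identical data: positive on Day 7, negative on Day 14.

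**Working it through.** The protocol states no figure for this point, so there is none to reproduce. The check is a comparison of days, followed by an illustration of what the gap holds.

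**1. Days side by side**

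| Place | Days |
|---|---|
| Outcome: Synopsis, Section 5 | 7, **10**, 14, 28 |
| Viral samples: Table 1, footnote 2 | 0, 2, 4, 6, 7, 14, 28 |
| Analysis: Section 12 | 7, 14, 28 |
| Sparse PK: Section 13 text | 3, 7, **10**, 21, 28 |
| Sparse PK (dried blood spot): Section 13 table | 2, 4, 6, 7, 14, 28 |

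Outcome days without a viral sample: {7, 10, 14, 28} minus {0, 2, 4, 6, 7, 14, 28} = {10}. Section 12's days are all sampled.

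The Section 13 text is the only hint of a Day 10 specimen. It does not rescue the outcome, because it concerns PK, conflicts with its own table, and has no Day 10 mark in the PK row of Table 1. The dried-blood-spot days in the Section 13 table match the post-baseline viral sampling days exactly, as footnote 3 would lead one to expect.

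**2. Gaps between successive viral samples**

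0–2: 2 days; 2–4: 2; 4–6: 2; 6–7: 1; 7–14: 7; 14–28: 14. A Day 10 sample would split the 7-day gap into 3 + 4.

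**3. Share of participants converting in each gap**

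The protocol gives no control median for clearance, so this step is assumption. Let clearance be exponential with control median *m* and hazard ratio *h*:

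S(t) = 2^(−h·t/m), and the share converting in (a, b] = S(a) − S(b).

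The grid was *m* = 5, 7, 10, 12, 14 days and *h* = 1.0, 1.6, 1.8. The upper two values of *h* are one reading of the 60–80% improvement in Section 6. Figure 3 is not shown, so the intended effect measure is uncertain.

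- Days 7–14, lowest: *m* = 5, *h* = 1.8, share 0.144. Highest: *m* = 7, *h* = 1.0, 0.500 − 0.250 = 0.250.
- Days 6–7, lowest: *m* = 14, *h* = 1.0, share 0.036. Highest: *m* = 7, *h* = 1.6, share 0.057.

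So 14–25% of participants convert in the unsampled week, against about 4–6% in the one day between the adjacent samples.

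For Days 14–28 under the same model with *h* = 1.0: *m* = 7 gives 0.250 − 0.0625 = 0.1875, and *m* = 12 gives 0.445 − 0.198 = 0.247.

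**4. Does the gap cost power?**

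Log-rank test on visit-observed times, 89 participants, two-sided 5%, 3,000 simulated trials per cell:

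| Control median | HR | As scheduled | Day 10 added |
|---|---|---|---|
| 7 | 1.6 | 54.2% | 55.5% |
| 10 | 1.6 | 52.5% | 52.4% |
| 14 | 1.6 | 49.7% | 49.9% |
| 7 | 1.8 | 75.0% | 75.2% |
| 10 | 1.8 | 70.5% | 72.8% |
| 14 | 1.8 | 69.0% | 69.6% |

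The differences run from −0.1 to +2.3 points. The standard error of one cell is about √(0.5 × 0.5 / 3000) = 0.9 points, so about 1.3 points for a difference. The columns are what matter here. The absolute levels depend on the assumed effect and should not be read as a check of the sample size.

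**The case against.** The strongest reply is that sampling and analysis already agree. Table 1, footnote 2 and Section 12 are consistent with one another, and Day 10 is a stray entry in the Synopsis and Section 5. Deleting it makes the PCR outcome consistent, and nothing compels a new schedule. This stands. Deletion is a valid reconciliation, and a Day 10 sample is a design choice. It does not remove the point, because the primary outcome still promises a result that cannot be obtained.

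Three stronger readings are tempting, and the protocol does not support them.

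- **Reading 7 and 12 days as the expected clearance medians.** Section 1.1 gives these figures for another regimen, compared with lopinavir/ritonavir, after a list of three outcomes and with a hazard ratio of 4.37. Under an exponential model 12/7 = 1.71, which does not match 4.37. They cannot show where conversions in this trial will fall, so a range of medians is used above.
- **Concluding that every conversion in the gap will be dated to Day 14, so that medians are distorted.** The protocol states no dating rule for time to PCR negativity, and a separate analysis plan could treat the times as interval-censored. The loss of resolution is certain; a particular bias in the median is not.
- **Concluding that the gap weakens the test.** The simulation, which does date conversions to the next visit, shows almost no change.

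The gap should also be kept in proportion. The interval from Day 14 to Day 28 is twice as long, holds a similar share of conversions in the cases worked, and is not shortened by a Day 10 sample. Removing the Day 6 specimen would also take an early point from another primary outcome, the viral-load pattern over time.

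**Conclusion.** The contradiction is established from the text alone and needs no assumption: one of the four stated primary PCR time points has no scheduled specimen and is absent from the analysis section. It should be settled before sampling, since missed specimens cannot be recovered.

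The coarse timing between Days 7 and 14 is also a fact of the schedule. Its size, 14–25% of participants, rests on exponential clearance and on assumed medians and hazard ratios. The harm is an unobservable primary time point and poor resolution of the endpoint behind the sample size. It is not a material loss of power. A reader might infer that the schedule must be rebuilt; the documents require only that the stated days agree.

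**What to change.** Make the Synopsis, Section 5, Table 1 with footnotes 2 and 3, Section 12 and Section 13 list the same days. Either route will do.

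- **(a) Schedule a Day 10 viral sample.** Add it to Table 1 and footnote 2, and add Day 10 to Section 12. Moving the Day 6 sample gives Days 0, 2, 4, 7, 10, 14 and 28, still seven samples. The paired sparse PK entries must move too: the PK row of Table 1 and the Day 6 dried blood spot in Section 13. The cost is one early viral-load and PK point, with Day 7 still sampled. Table 1 already has Day 10 assessments for vital signs, Flu-PRO, clinical improvement and adverse events. Adding Day 10 while keeping Day 6 avoids that loss at the price of one extra specimen per participant.
- **(b) Delete Day 10 from the primary outcome** in the Synopsis and Section 5. This costs only wording and removes the contradiction, but leaves the 7-day gap.

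Under either route, reconcile the sparse PK days in the Section 13 text with the table beneath it. The Day 14 to 28 gap remains in both cases and should be acknowledged when time to PCR negativity is reported.

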## 3. Study Design

This is a pilot phase 2, open label randomised controlled trial. A total of 98 patients with confirmed COVID-19 diagnosis (defined as SARS-CoV-2 polymerase chain reaction (PCR) positive nasopharyngeal swab) will be recruited from participating treatment centres. Participants will be randomised to receive either the standard of care (SOC) plus nitazoxanide for 14 days, starting from day 1 or the SOC alone for 14 days.

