### **3.4. Follow-up**

The treatment duration for participants in the intervention group will be 14 days. However, follow up will continue until day 28 after study entry at the end of which all participants will exit the study. The schedule of activities during the follow up period is presented in Table 1. Participants who stop study product should continue study participation off study product with continued evaluations as per the schedule of activities. The reason for study product discontinuation should be recorded. Daily survey, vital signs and SpO2 as well as Flu-PRO questionnaire will be recorded by participant (both on paper and cloud-based forms using their mobile device while connected to the internet). SpO2 will be measured after at least 5 minutes resting in a sitting or supine position. Participants with an SpO2 below 93% will repeat the assessment 2 hours later. If the repeat assessment is still below 93%, study clinician will be alerted.

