## **17.2. Withdrawal from the trial**

Although a participant is not obliged to explain their reason for withdrawing prematurely from a trial, reasonable effort will be made to ascertain the reason while fully respecting the participant's rights. Additionally, the investigators may withdraw a participant from the trial for any of the following reasons:

- Decision of the ethics committees or the regulatory agency as part of their duties, clinical investigators or primary care providers if they think continued participation is no longer in the best interest of the participant.
- If failure to comply with the protocol requirements by the participant puts them or the reliability of resulting data at risk.
- If a participant leaves the isolation and treatment centre (study site) against medical advice, they will be considered lost to follow-up and the following actions will be taken:
  - The site clinical investigator (or a designated member of the study team) will attempt to contact the participant as soon as possible and counsel the participant on the need to follow the national COVID-19 case management guidance.
  - The caller will ascertain whether or not the participant wishes to continue in the trial and return to the isolation and treatment centre to facilitate this. Arrangement to return participants to site will be as per existing SOP of the NCDC.
  - Where possible, up to 2 telephone call attempts per day must be made to the participants usual mobile number or their next of kin (if necessary) in the 3 days following a participant's absence from site before a participant will be deemed lost to follow-up. A participant who is unreachable after these efforts will be withdrawn from the study due to lost to follow-up.

Any data collected before such withdrawal of consent will be retained and used. Withdrawing participants will have the right to request destruction of any samples taken and not yet tested. Such requests will be documented by the site investigator. Whenever possible, follow up assessments scheduled for day 28 study exit visit will be completed at the time of withdrawal or discontinuation.

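### Time to death and survivor-only hospital stay are poorly defined for a randomised comparison, and Section 17.2's early Day 28 assessment conflicts with Section 3.4

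*Protocol*

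**What the plan says.** Protocol Section 5 lists two secondary outcomes that matter here: "Time from treatment initiation to death" and "Duration of hospitalization in survivors". The same section times the primary clinical outcome differently: it is "defined as time from randomization to either an improvement of two points on a 10-category ordinal scale" or discharge, whichever is earlier. Day 28 mortality is a separate secondary outcome.

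Section 3 describes the study drug as "starting from day 1 or the SOC alone for 14 days". Table 1 marks randomisation and dispensing of standard of care on Day 0, and trial drug from Day 1.

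On follow-up, Section 3.4 states: "Participants who stop study product should continue study participation off study product with continued evaluations as per the schedule of activities". Section 17.1, headed *Discontinuation*, deals only with stopping study treatment and says such patients may continue with evaluations. Section 17.2, on withdrawal from the trial, ends: "Whenever possible, follow up assessments scheduled for day 28 study exit visit will be completed at the time of withdrawal or discontinuation". In Table 1 the Day 28 column includes the saliva or swab sample for SARS-CoV-2. PCR negativity at Day 28 is part of a primary outcome in Section 5 and is compared between arms in Section 12.

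**The concern.** A randomised comparison needs the same clock and the same patients in both arms.

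- **Time to death.** No treatment start is defined for a patient on standard of care alone. A patient randomised to drug who dies before the first dose has no study-drug start at all.
- **Hospital stay in survivors.** Survival is itself an outcome that treatment may change. If the drug keeps very sick patients alive, they join the survivor group on that arm only and lengthen its mean stay. A beneficial drug can then look worse.
- **Early Day 28 assessment.** If *discontinuation* in Section 17.2 covers stopping study drug, only the intervention arm can trigger it. A sample taken in the first two weeks could then stand as a Day 28 result in that arm alone.

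A larger sample removes none of these.

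**Working it through.** The protocol gives no figure for these outcomes, so there is none to reproduce; its sample-size calculation concerns time to PCR negativity and does not bear on this point. All rates below are assumptions used to show size. The 49 per arm is from the synopsis.

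**1. Clock for time to death.** Randomisation is on Day 0 and drug starts on Day 1, so the offset is about 1 day. With 28-day mortality m and a constant hazard, expected deaths per arm between Day 0 and Day 1 are 49 × [1 − (1 − m)^(1/28)]:

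- m = 5%: 0.09
- m = 10%: 0.18
- m = 20%: 0.39

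That is 0.1 to 0.4 deaths per arm, so the effect is small.

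**2. Stay in survivors.** Let control mortality be m, halved to m/2 on drug. Patients who would survive on either arm stay 12 days on both, so there is no true effect on stay. Patients saved by the drug stay L days. Control survivors average 12. Drug survivors average [(1 − m) × 12 + (m/2) × L] / (1 − m/2), so the difference is (m/2)(L − 12)/(1 − m/2) days:

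| Control mortality | L = 16 | L = 20 | L = 24 |
|---|---|---|---|
| 5% | 0.10 | 0.21 | 0.31 |
| 10% | 0.21 | 0.42 | 0.63 |
| 20% | 0.44 | 0.89 | 1.33 |

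Smallest case: 0.025 × 4 / 0.975 = 0.10. Largest: 0.10 × 12 / 0.90 = 1.33. In every cell the arm with fewer deaths shows the longer stay.

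**3. Early Day 28 assessment.** The passages side by side:

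| Section | After stopping study drug |
|---|---|
| 3.4 | Should continue, on the schedule |
| 17.1 | May continue |
| 17.2 | Day 28 assessments done at withdrawal or discontinuation, where possible |

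Section 17.2 names withdrawal and discontinuation as alternatives, directly after a section that uses *Discontinuation* for stopping treatment. A site could therefore take it to include stopping drug. If it did, and the early sample were analysed as Day 28, the error in the intervention arm's Day 28 negative proportion would be d × (P28 − Pt). Here d is the share who stop early, Pt the proportion negative when they stop and P28 the proportion negative at Day 28. None of the three is in the protocol.

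**The case against.** **Time to death.** The wording is treatment initiation, not study-drug initiation. Standard of care is dispensed to everyone on Day 0, so a common origin could be read in. That is fair, and a clock that differs by arm is therefore a possible reading rather than a stated rule. What stands is that the origin is left undefined and is not the one used for the primary outcome.

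**Stay in survivors.** This is one secondary outcome in a pilot of 98. Mortality is reported alongside it, and the primary outcome counts discharge without restricting to survivors. This limits the weight of the point, but does not make survivor stay a comparison of the groups as randomised.

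**Early assessment.** The sentence sits under trial withdrawal, is qualified by feasibility and does not say drug discontinuation. Section 16.1 separates leaving the study from stopping study treatment, so the bare word could mean leaving the study. This largely stands: the documents show a conflict to reconcile, not a rule that Day 28 data are taken early on drug.

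Four stronger readings are tempting and not supported:

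- A reader might put a figure on the PCR bias. For example, 5 or 10 of 49 stopping at Day 5, with exponential clearance at a median of 12 days, gives 25% negative at Day 5 and 80% at Day 28, hence 5/49 × 0.55 = 5.6 or 10/49 × 0.55 = 11 points. The stopping rate, stopping day and clearance curve are all assumed, and nothing says the early sample is labelled Day 28 or that sampling then ends.
- A reader might infer from the ground "If failure to comply with the protocol requirements by the participant puts them or the reliability of resulting data at risk" that withdrawals fall mainly on the drug arm. Protocol requirements such as diaries, vital signs and sampling bind both arms, and withdrawal on this ground is discretionary.
- A reader might extend the harm to ordinal-scale status at Day 28. Section 5 lists that status on Days 7 and 14 only.
- A reader might conclude that none of these outcomes is a randomised comparison. Day 28 mortality remains one if vital status is collected to Day 28. Day 28 PCR remains one if Section 3.4 is followed, and the clock for death can simply be defined.

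**Conclusion.** The point holds in three limited parts.

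1. The origin for time to death is undefined in one arm and for undosed patients. This is a real defect of definition with a small effect: about one day, or 0.1-0.4 deaths per arm at assumed mortality of 5-20%.
2. Hospital stay in survivors conditions on a post-randomisation event. The distortion is 0.1-1.3 days against the drug if mortality is halved from 5-20% and saved patients stay 16-24 days against 12. The direction follows from the definition whenever the drug saves patients with longer stays; the size rests on those assumptions.
3. Sections 3.4, 17.1 and 17.2 do not agree on what happens to Day 28 assessments after study drug is stopped. This part could touch a primary outcome, but only if Section 17.2 is read to cover drug discontinuation and the early sample is used as Day 28. Its size cannot be fixed from the documents.

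The changes are worth making because they remove avoidable bias at almost no cost. They do not call the whole outcome set into question.

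**What to change.** - **Section 5, death:** time death from randomisation, in all randomised patients.
- **Section 5, hospital stay:** compare days alive and out of hospital to Day 28, with death scored 0, in all randomised patients; or analyse time to discharge with death as a competing event. Stay in survivors can be kept as a descriptive figure.
- **Sections 3.4, 17.1 and 17.2:** reconcile them so that the early exit assessment applies only to withdrawal from the trial. Record it under its true date and never as Day 28. Seek Day 28 status for everyone who has not withdrawn consent. This concerns data collection only and leaves the rules for stopping treatment untouched.

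The cost is a few lines of wording and a Day 28 contact, by telephone if necessary, for a small number of patients. Days alive and out of hospital is slightly less familiar to readers than length of stay.
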